**Approved on**  
**October 22, 2025**

## 1. Annexure: A – Ethical Statement Checklist

**Put a tick sign (✓) appropriate answers against each of the following statements (If not Applicable, please write N/A)**

### 1. Source of Population:

- a) Patients ☒ Yes ☐ No
- b) Healthy Subjects ☒ Yes ☐ No
- c) Minors or persons under guardianship ☒ Yes ☐ No

### 2. Does the study involve:

- a) Physical risks to the Subjects ☐ Yes ☒ No
- b) Social Risks ☐ Yes ☒ No
- c) Psychological risks ☐ Yes ☒ No
- d) Discomfort to the subject ☐ Yes ☒ No
- e) Invasion of the body ☐ Yes ☒ No
- f) Invasion of Privacy ☐ Yes ☒ No
- g) Disclosure of information damaging to the subject or others ☐ Yes ☒ No

### 3. Does the study involve:

- a) Use of records: - (Hospital, Medical, Death, Birth, or other) ☒ Yes ☐ No
- b) Use of fetal tissues
- c) or abortus ☒ Yes ☐ No
- Use of organs or body fluids ☐ Yes ☒ No

### 4. Will subjects inform about:

- a) Nature and purposes of study ☒ Yes ☐ No
- b) Procedures to be followed including alternative used ☒ Yes ☐ No
- c) Physical risks ☒ Yes ☐ No
- d) Private questions ☒ Yes ☐ No
- e) Mental risks ☒ Yes ☐ No
- f) Benefits to be derived ☒ Yes ☐ No
- g) Right to refuse to participate or to withdraw from study ☒ Yes ☐ No
- h) Confidential handling of data ☒ Yes ☐ No
- i) Compensations: (where there are risks or loss of working time or privacy is involved in any particular procedure) ☐ Yes ☒ No

### 5. A signed consent form will be obtained:

- a) From Subjects (If adult) ☒ Yes ☐ No
- b) From parent or guardian ☒ Yes ☐ No

### 6. Will precautions be taken to protect the anonymity of subjects?

- ☒ Yes ☐ No

## 2. Annexure: B – Research Methodology

|                             |                                                                                                                                                                                                                                                                                                                                                                                                                                                                                                                                                                                                                                                                                                                                                                                                                                                                       |
|-----------------------------|-----------------------------------------------------------------------------------------------------------------------------------------------------------------------------------------------------------------------------------------------------------------------------------------------------------------------------------------------------------------------------------------------------------------------------------------------------------------------------------------------------------------------------------------------------------------------------------------------------------------------------------------------------------------------------------------------------------------------------------------------------------------------------------------------------------------------------------------------------------------------|
| Research Title       | Effectiveness of a Five-Component Multimodal Intervention on Executive Function in Children with Autism Spectrum Disorder: A Randomized Controlled Trial                                                                                                                                                                                                                                                                                                                                                                                                                                                                                                                                                                                                                                                                                                              |
| Eligibility criteria | Qualified health professionals will recruit participants through an impartial screening process that adheres to predefined inclusion and exclusion criteria. Children aged 4–18 years of both sexes with a confirmed ASD diagnosis according to DSM-5 and CARS-2, assessed by a child psychiatrist, and who consent to participate in a 12-week intervention will be included. Participants will be excluded if they have cerebral palsy, Down syndrome, ADHD, or any recent (past six months) muscle injury, sprain, head injury, skin laceration, or other conditions that may hinder exercise or study outcomes. Children in the healthy control group will undergo the same interview to confirm typical development and will complete the same outcome measures to compare whether the ASD group can achieve normal developmental levels after the intervention. |
| Study setting        | Paediatrics laboratory within the Department of Physiotherapy and Rehabilitation at Jashore University of Science and Technology, and Proyash, Jashore, Bangladesh.                                                                                                                                                                                                                                                                                                                                                                                                                                                                                                                                                                                                                                                                                                   |
| Date of recruitment  | 10/12/2025                                                                                                                                                                                                                                                                                                                                                                                                                                                                                                                                                                                                                                                                                                                                                                                                                                                            |
| Study method         | Randomized Controlled Trial                                                                                                                                                                                                                                                                                                                                                                                                                                                                                                                                                                                                                                                                                                                                                                                                                                           |
| Reporting guideline  | CONSORT                                                                                                                                                                                                                                                                                                                                                                                                                                                                                                                                                                                                                                                                                                                                                                                                                                                               |
| Intervention details | All participants will receive a healthy-lifestyle guideline booklet to follow throughout the 24-week study. The wait-list control group will receive these guidelines plus biweekly discussion sessions during their initial 12-week period and will later receive the same intervention as the experimental group. The experimental group will complete a 12-week, five-component multimodal program delivered by trained physiotherapists, with                                                                                                                                                                                                                                                                                                                                                                                                                     |

**Institutional Review Board (IRB)**  
**Department of Physiotherapy & Rehabilitation**  
**Jashore University of Science & Technology**

mail: [[contact]](mailto:[contact]) website: <https://ptr.just.edu.bd/>

|                              |                                                                                                                                                                                                                                                                                                                                                                                                                                                                                                                                                                                                                                                                                                                                                                                                                                                                 |
|------------------------------|-----------------------------------------------------------------------------------------------------------------------------------------------------------------------------------------------------------------------------------------------------------------------------------------------------------------------------------------------------------------------------------------------------------------------------------------------------------------------------------------------------------------------------------------------------------------------------------------------------------------------------------------------------------------------------------------------------------------------------------------------------------------------------------------------------------------------------------------------------------------|
|                              | all procedures, dosages, and progressions monitored by four research assistants for consistency. Each 60-minute session, conducted five times per week in small groups, will include yoga (10 minutes), aerobic exercise (15 minutes), strengthening exercises (10 minutes), neurocognitive tasks (15 minutes), and music-based mindfulness (10 minutes), with structured rest intervals and progressive adjustments based on individual abilities. Detailed intervention content is presented in a supplementary file. A follow-up assessment will occur 12 weeks after the intervention to evaluate sustained effects, during which all participants will continue following lifestyle guidelines, and the control group will undergo the experimental intervention, accompanied by two discussion sessions addressing the health needs of children with ASD. |
| Intervention provider | Experienced and qualified health professionals                                                                                                                                                                                                                                                                                                                                                                                                                                                                                                                                                                                                                                                                                                                                                                                                                  |
| Outcome measurement   | 
Primary outcomes
 
The primary outcome will be Executive Function, assessed through three subcomponents: Inhibitory Control, Cognitive Flexibility and Working Memory. Inhibitory Control (IC) will be measured using the Go/No-Go (GNG) task; Cognitive Flexibility will be assessed with the Trail Making Test (TMT); Working Memory (WM) will be evaluated using the Corsi Block Tapping Task (CBTT), Forward Digit Span (FDS) test, and Backward Digit Span (BDS) test.
 
Secondary outcomes
 
The secondary outcomes will be social responsiveness and autism-related behavioral changes. Social responsiveness will be assessed using the Social Responsiveness Scale, Second Edition (SRS-2), and ASD-related characteristics will be evaluated using the Autism Treatment Evaluation Checklist (ATEC)
               |
| Statistical analysis  | Statistical analysis will be conducted using SPSS version 26. Continuous variables will be summarized as mean $\pm$ standard deviation (SD), and categorical variables as frequencies and percentages. Baseline differences across the three groups (two ASD intervention groups and healthy controls) will be examined using one-way ANOVA for normally distributed variables and                                                                                                                                                                                                                                                                                                                                                                                                                                                                              |

IRB of the Department of Physiotherapy and Rehabilitation established on March 27, 2024 and was approved by the departmental academic committee meeting resolution.

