## Institutional Review Board (IRB)

Department of Physiotherapy & Rehabilitation

Jashore University of Science & Technology

mail: [[contact]](mailto:[contact]) website: <https://ptr.just.edu.bd/>

Kruskal–Wallis tests for non-normally distributed data. Primary intervention effects across three assessment points (T1, T2, T3) will be evaluated using linear mixed-effects models (LMMs), with group specified as the between-subjects factor and time as the within-subjects factor, and pre-specified baseline covariates (age, sex, and body mass index). All covariates were measured at baseline prior to randomization and were included based on their known associations with executive function; post-randomization or time-varying covariates were not adjusted for to avoid mediation or over-adjustment bias. Although sample size estimation was based on mixed-model ANOVA, LMMs were selected for primary analysis due to their robustness to missing data and flexibility in modelling repeated measures. Model assumptions, including normality and homoscedasticity, will be assessed, and robust or rank-based alternatives will be applied if violations are detected. Significant group  $\times$  time interactions will be explored using simple main effects with Holm–Bonferroni correction for multiple comparisons. Effect sizes will be reported as partial  $\eta^2$  for mixed models and Cohen’s  $d$  (pooled SD) for pairwise comparisons, interpreted using conventional benchmarks. Within-group changes across time points will be examined using paired-samples  $t$ -tests, interpreted in relation to both statistical significance ( $p < 0.05$ ) and established minimal clinically important differences (MCID) where available. To control family-wise error across multiple primary outcomes, Holm–Bonferroni adjustment will be applied. Missing data will be handled under the assumption of missing at random (MAR) using an intention-to-treat approach with multiple imputation. Sensitivity analyses will be performed to explore the potential impact of outcome-dependent exclusions, such as participants with fewer than 50% correct responses on Go trials. Multivariate relationships among primary outcomes will be further examined using multivariate analysis of covariance (MANCOVA), adjusting for baseline covariates and assessing assumptions of multivariate normality and homogeneity of covariance matrices. This analytical strategy ensures robust, unbiased, and clinically interpretable inference in longitudinal, multigroup studies.

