**6. Annexure: F – Intervention Tracking Sheet/Checklist**  
**7. (Put a tick ✓)**

| Patient ID | Group | Start date | Intervention Timeline
Session: 1 to 60 | End date | Any comments |
|------------|-------|------------|-------------------------------------------|----------|--------------|
|            |       |            |                                           |          |              |

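### The programme is delivered in small groups, but the primary mixed model names no therapy-group or therapist term and the tracking sheet has no dedicated field for either

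*Protocol*

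**What the plan says.** **Delivery.** The Intervention details row of Annexure B describes a 12-week "five-component multimodal program delivered by trained physiotherapists", with "Each 60-minute session, conducted five times per week in small groups, will include yoga (10 minutes" opening the list of components. The number and size of the groups, whether a child stays in one group, and how physiotherapists are assigned to groups are not stated.

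**Comparator.** Up to T2: "The wait-list control group will receive these guidelines plus biweekly discussion sessions during their initial 12-week period". Between T2 and T3, "the control group will undergo the experimental intervention".

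**Primary analysis.** The Statistical analysis row of Annexure B specifies "linear mixed-effects models (LMMs), with group specified as the between-subjects factor and time as the within-subjects factor", plus "pre-specified baseline covariates (age, sex, and body mass index". The reasons given for choosing this model are missing data and repeated measures. Neither therapy group nor therapist appears in the model, in the named sensitivity analysis, or in the mixed-model ANOVA cited as the sample-size basis.

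**Data capture.** The Annexure F tracking sheet has columns for patient ID, group, start date, sessions ("Intervention Timeline Session: 1 to 60"), end date and comments. The group column most naturally means trial arm, since the adverse effect checklist in Annexure G has the same column. Neither form has a separate column for therapy group or provider.

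**The concern.** Children are randomised individually, but in the experimental arm treatment reaches them in groups, five days a week for 12 weeks. Children who train together under the same physiotherapist may come to resemble each other in outcome through group dynamics, therapist skill and the pace of progression. Until T2 the wait-list arm has only the booklet and the discussion sessions. That is a partially nested design.

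A model with arm, time and child-level covariates treats children as independent once those terms are fitted. Any positive correlation within therapy groups then makes the standard error of the arm contrast too small and its p-value too low, so the error favours a false positive. The planned Holm–Bonferroni adjustment takes the p-values as they come and cannot correct this.

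The data-capture side matters as much. No later analysis plan can model group membership that was not recorded.

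**Working it through.** The protocol gives no sample size, power, effect size, group size or ICC, so it has no figure to reproduce. The sizes below are illustrations under stated assumptions.

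**Inputs**
- From the protocol: small-group delivery in the experimental arm before T2; the same programme for the wait-list arm between T2 and T3; a 0.05 significance level (stated beside the paired t-tests).
- Assumed: two equal arms; two-sided tests; therapy groups of fixed membership with m = 4 to 8 children; ICC = 0.02 to 0.15, meaning the correlation within a therapy group of the outcome as analysed at that visit; no correlation among wait-list children before T2.

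**Formulas**
- Design effect in a group-treated arm: DE = 1 + (m − 1) × ICC.
- True SE / model SE at T2, one arm clustered: R2 = √[(1 + DE)/2].
- True SE / model SE at T3, both arms clustered: R3 = √DE.
- Actual two-sided alpha: 2 × [1 − Φ(1.960/R)].

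**One case in full (m = 6, ICC = 0.10)**
- DE = 1 + 5 × 0.10 = 1.50.
- T2: R2 = √(2.50/2) = √1.25 = 1.118; 1.960/1.118 = 1.753; alpha = 0.0796.
- T3: R3 = √1.50 = 1.225; 1.960/1.225 = 1.600; alpha = 0.1095.

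**Range at T2**

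| m | ICC | DE | R2 | Alpha |
|---|---|---|---|---|
| any | 0 | 1.00 | 1.000 | 0.0500 |
| 4 | 0.02 | 1.06 | 1.015 | 0.0535 |
| 4 | 0.05 | 1.15 | 1.037 | 0.0587 |
| 6 | 0.05 | 1.25 | 1.061 | 0.0646 |
| 6 | 0.10 | 1.50 | 1.118 | 0.0796 |
| 8 | 0.10 | 1.70 | 1.162 | 0.0916 |
| 8 | 0.15 | 2.05 | 1.235 | 0.1125 |

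The true SE is therefore 1.5% to 23% larger than the model SE. Put the other way, the model SE is too small by 1 − 1/1.015 = 1.5% to 1 − 1/1.235 = 19%.

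**Check by simulation.** Data with one clustered arm and no true effect were analysed with an ordinary two-sample t-test, 40,000 replicates per setting. The rejection rate was 0.078 for m = 6, ICC = 0.10 with 30 children per arm (formula 0.0796), 0.091 for m = 8, ICC = 0.10 with 48 per arm (formula 0.0916), and 0.050 for m = 5, ICC = 0 with 30 per arm. The numbers per arm are also assumptions.

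**Which model term would help.** Suppose the outcome of child i in therapy group g at time t contains a group effect that is constant over time, u(g). The change from T1 to T2 then contains u(g) − u(g) = 0, so this term drops out of the group × time contrast and leaves its standard error unchanged. Correlation caused by shared treatment behaves differently: it is absent at T1, before treatment, and present at T2. It needs a term w(g, t) that is free to differ between baseline and later visits, because w(g, T2) − w(g, T1) does not cancel.

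**The case against.** **An analysis plan could settle this.** The protocol does not write out its random effects, and detail of that kind is commonly left to the SAP, which is not at hand. That stands as a limit on the claim: the exact statement is that the protocol names no such term, not that the final analysis will certainly lack one. It does not remove the point. The protocol does state its primary model, factors and covariates, and these do not match its own mode of delivery. The recording form is a protocol document that an SAP cannot repair afterwards.

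**Clustering may be weak or absent.** Membership or physiotherapists may rotate, progression is adjusted to the individual child, and four research assistants monitor consistency. All of this could keep the ICC low, and at m = 4, ICC = 0.02 the effect is negligible. This stands, and it makes the finding conditional.

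**Stronger readings that a reader might infer, and that the documents do not support:**
- *The confidence intervals are too narrow, and type I error is above nominal on every primary outcome.* This needs an ICC above zero and reasonably stable groups. The protocol gives neither, and it mentions no confidence intervals; it reports p-values, partial η² and Cohen's d.
- *The same children train together under the same physiotherapists for all 60 sessions.* The protocol says small groups and trained physiotherapists, and no more.
- *The model SE is up to 23% too small.* The true SE is up to 23% larger, which makes the model SE up to 19% too small.
- *Only the experimental arm is affected.* That fits T2. By T3 the wait-list arm has had the same programme.
- *One extra random intercept cures it.* As shown above, a time-constant one leaves the group × time standard error as it was.

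**Conclusion.** The point holds in conditional form. The omission is clear from the text: small-group delivery, a stated primary model with no therapy-group or therapist term, and a tracking sheet with no dedicated field for either. Confidence in the omission is high.

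Confidence in its size is moderate at best, because group size, stability of membership and ICC are all assumed. Over the assumed range, the consequence at T2 runs from negligible to an alpha of more than twice nominal. The middle case (m = 6, ICC = 0.10) gives about 0.080 at T2, and about 0.110 at T3 if both arms are clustered. If the ICC is zero, nothing is lost.

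This should be changed. The possible error favours a false positive, the remedy is cheap, and recording is best in place before the first session.

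**What to change.** 1. **Record.** Add a therapy-group ID and a lead-physiotherapist ID to Annexure F, for both arms, from each arm's first programme session. Define the existing group column as trial arm if that is what it means. If a child changes group, record the change.
2. **State.** Give the group size and say whether membership is fixed.
3. **Model.** Account for therapy group with a term that acts on post-baseline outcomes, by one of two routes:
   - in the three-visit mixed model, a therapy-group-by-time random effect;
   - a baseline-adjusted model for T2, with a therapy-group random effect in the experimental arm and each wait-list child as its own cluster, extended to the wait-list therapy groups at T3.
4. **Inference.** Use small-sample degrees of freedom, or cluster-robust standard errors with a small-sample correction, since the number of therapy groups is likely to be small.

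**Cost.** One or two columns on an existing form and a modest change to the model. Standard errors and p-values will be somewhat larger, and correctly so, and some power is lost against a calculation that ignored clustering. For example, if 80% power had been planned (an assumption, as the protocol states none), then at m = 6, ICC = 0.10 the power at T2 would be Φ(2.802/1.118 − 1.960) = Φ(0.546), about 71%. The sample-size basis should be checked against this.
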